### Participant selection and enrolment

Eligible patients will be identified by the usual clinical care team in the emergency department or an equivalent acute medical admissions unit or using the electronic medical records after discharge. To ensure that our trial is inclusive and representative of the broad patient population presenting to hospital with suspected acute coronary syndrome, potential participants who are not approached in hospital (e.g. due to out of hours attendance or study team being unavailable) will be identified using electronic medical records or through referral from the clinical team and contacted by telephone to invite them to take part in the study. For the duration of the study, the trial will be incorporated into the clinical pathway for the evaluation of patients with suspected acute coronary syndrome. As part of the standard of care clinical pathway, patients with suspected acute coronary syndrome who are discharged from the emergency department will receive an information leaflet. This contains information about chest pain, a summary of the study, contact details of the research team, and explains that potential participants might be contacted after discharge.

Patients who are consented in the hospital will be asked to provide written informed consent whilst patients who are contacted by telephone will be given the option to either attend a study visit to provide written informed consent in person or provide informed consent verbally over the telephone. All patients who are randomised to CTCA will have their consent reaffirmed at the scanning visit and will be asked to sign a consent form before any further research activities are carried out.

### Randomisation

Following consent, patients will be randomised (1:1), either to CTCA plus standard of care or standard of care alone. Randomisation will be conducted using a web-based computer-generated system to ensure allocation concealment, stratified by age (< 70 years versus ≥ 70 years), sex, site and previously diagnosed coronary artery disease. This is an open-label trial design, and the patient and clinical care team will not be blinded to the intervention. Once randomised, a letter will be sent to the participant’s general practitioner (GP) to inform them of their involvement in the study.

### Study assessments

Study participants who are randomised to standard of care will not have any further study visits. Those randomised to CTCA with standard of care will be invited for an outpatient CTCA as soon as possible after their initial hospital attendance (ideally within 4 weeks of randomisation).

### Initial hospital attendance, screening visit or telephone contact

During the initial emergency department or equivalent acute medical admissions unit attendance, study visit or telephone contact, the research team will review participants’ clinical history including cardiovascular risk factors, past medical history, standard clinical biochemical and haematological variables, high-sensitivity cardiac troponin concentrations and the 12-lead electrocardiogram. The Seattle Angina Questionnaire (SAQ-7) shortened Rose Angina and EQ-5D-5L questionnaires will also be administered at baseline.

### Scanning visit assessment

To optimise the quality of the CTCA scan images, participants with a heart rate greater than 60 beats per minute may be prescribed a beta-blocker, rate-limiting calcium channel antagonist or ivabradine to slow their heart rate, and sublingual glyceryl trinitrate will be administered according to local guidance. Prescribing, dispensing and administration of rate limiting medications will follow local protocol and procedures.

### Computed tomography coronary angiography

Participants randomised to CTCA will undergo electrocardiogram (ECG) gated CTCA using ≥ 64-multidetector scanner, according to the Society of Cardiovascular Computed Tomography guidelines. Prospective or retrospective ECG-gating will be used according to heart rate and local protocols [21]. Tube current, tube voltage and volume and rate of iodine-based contrast media will be optimised based on body-mass index. Cardiac and wide field-of-view reconstructions will be produced and transferred to post-processing software for analysis. Images will be reported according to the Society of Cardiovascular Computed Tomography guidelines [22]. Per segment assessment of the presence of atherosclerotic plaque and diameter stenosis will be performed. Diameter stenoses will be classified as normal or near normal (< 10%), mild (10–49%), moderate (50–70%) or obstructive (> 50% stenosis in the left main stem or > 70% stenosis in other coronary arteries). Incidental findings (cardiac non-coronary and extracardiac) on CT will be documented in clinical reports and notified to responsible clinicians as per local practice.

### Management recommendations

Following CTCA reporting, results will be reviewed by members of the research team as soon as possible and a report forwarded to the participant, primary care physician and other healthcare professionals involved in clinical care as appropriate (Fig. 1). In patients with normal or near normal (< 10% stenosis) coronary arteries, no specific action will be required. However, for patients with mild (10–49%) or moderate (50–70%) non-obstructive coronary artery disease, the report will include recommendations to commence secondary preventative medical therapy (statin therapy alone or a combination of antiplatelet and statin therapy, respectively). For patients found to have untreated obstructive coronary artery disease (> 50% stenosis in the left main stem or > 70% stenosis in other coronary arteries), the report will include recommendations to provide lifestyle advice and commence antiplatelet and statin therapy, if there are no contra-indications, and they will also be offered a cardiology outpatient consultation (either face to face or telephone based) in accordance with local NHS policy, ideally within 2 weeks of the CTCA scan result.

**Fig. 1 Fig1:**
[figure not shown]
Study design overview

### Adverse events

Patients attending the scanning visit will be asked to contact the research team if they experience any untoward effects within 48 h of the CTCA scan. The research team will assess seriousness, expectedness, severity and causality of the adverse event. All serious adverse events will be reported immediately or within 24 h to the sponsors.

### Long term follow-up assessments

All patients will be followed up until at least the required number of primary outcome events have accrued. This is expected to be a minimum of 24 months for each participant and a median of 36 months. Follow-up data will be collected remotely from medical records (and any future data linkage that may be necessary). Both the short version of the Seattle Angina Questionnaire (SAQ-7) and the European Quality of Life Five Dimension (EQ-5D-5L) questionnaire will be further administered at 3 months, 12 months and 24 months after randomisation. The SAQ-7 questionnaire has been validated in patients with coronary artery disease and shown to be sensitive to therapeutic interventions [23]. The EQ-5D-5L is a validated questionnaire measuring self-reported health status over time [24]. A lifestyle questionnaire recording body mass index, physical activity, smoking, diet, blood pressure, cholesterol and blood glucose will be administered together with the SAQ-7 and EQ-5D-5L questionnaires 24 months after randomisation (Table 2).

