**Methods:**

TARGET-CTCA is a multicentre prospective randomised open label with blinded endpoint parallel group event driven trial. After myocardial infarction and clear alternative diagnoses have been ruled out, participants with intermediate cardiac troponin concentrations (5 ng/L to 99th centile upper reference limit) will be randomised 1:1 to outpatient CTCA plus standard of care or standard of care alone. The primary endpoint is myocardial infarction or cardiac death. Secondary endpoints include clinical, patient-centred, process and cost-effectiveness. Recruitment of 2270 patients will give 90% power with a two-sided *P* value of 0.05 to detect a 40% relative risk reduction in the primary endpoint. Follow-up will continue until 97 primary outcome events have been accrued in the standard care arm with an estimated median follow-up of 36 months.

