### Secondary endpoints

The secondary endpoints include clinical, patient-centred, process and cost-effectiveness. These are detailed in Table 1.

**Table 1 Tab1:** Secondary endpoints

1. Clinical and patient-centred endpoints	• Myocardial infarction • Cardiac death • Cardiovascular death • Non-cardiovascular death • All-cause death • Unscheduled urgent coronary revascularisation • Hospital reattendance with suspected acute coronary syndrome • Proportion of patients with major bleeding (BARC 3–5) • Symptomatic status as assessed by the short form Seattle Angina Questionnaire (SAQ-7) up to 24 months of randomisation • Quality of life as assessed by the EQ-5D-5L up to 24 months of randomisation • Lifestyle changes including diet, smoking habit, and exercise at 24 months
2. Process endpoints	• Proportion of patients with allergy, anaphylaxis or acute kidney injury following study CTCA scan • Proportion of patients with clinically significant abnormal non-cardiac findings on study CTCA scan • Radiation dose from study CTCA scan • Proportion of patients undergoing non-study CTCA or invasive coronary angiography within 90 days of hospital attendance • Proportion of patients undergoing non-invasive stress test within 90 days of hospital attendance
3. Cost effectiveness endpoints	• Proportion of patients prescribed therapies for coronary artery disease • Proportion of patients undergoing non-invasive stress testing • Proportion of patients undergoing coronary revascularisation • Incremental cost per quality-adjusted life year (QALY) gained

*Abbreviations*: *BARC* Bleeding Academic Research Consortium definition of bleeding [20], *CTCA* computed tomography coronary angiogram

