### Sample size calculation

Based on the event rate in the High-Sensitivity Troponin in the Evaluation of patients with suspected Acute Coronary Syndrome (High-STEACS) trial [19], myocardial infarction or cardiac death will occur in 7.2% of the study population at 24 months. The Scottish COmputed Tomography of the HEART (SCOT-HEART) trial [25] reported a 41% reduction in fatal and non-fatal myocardial infarction in those randomised to CTCA (hazard ratio 0.59 [95% CI: 0.41 to 0.81]), with the treatment effect of the intervention apparent at 36 months. It is anticipated that at a median follow-up of 36 months the event rate in the standard of care arm will be 9%. In the proposed study, for 90% power at an alpha of 0.05, 1081 participants will be required in each arm to detect a 40% relative risk reduction in the primary composite endpoint. To account for drop out of 5%, the aim is to recruit at least 2270 patients to the study. With this sample size, there will be 81% and 67% power to detect a 35% and 30% relative risk reduction if the intervention is less effective. Likewise, the sample size would have 99% power to detect a 50% relative risk reduction if CTCA is as effective in the study population as in those with stable chest pain [26]. With this sample size, it is estimated that 97 primary outcome events will be accrued in the standard care arm of the trial at a median follow-up of 36 months. The data monitoring committee (DMC) will review all primary outcome events intermittently and will inform the trial steering committee (TSC) when this target has been met.

On April 25, 2022, a blinded assessment of the number of events accrued in the first 1925 participants was undertaken and the DMC concluded the trial would not reach the number of primary outcome events required by the planned follow-up date of September 2024. This was a consequence of interruptions to recruitment due to COVID-19 with most participants having less than 12 months follow-up at this point. To minimise the likelihood that follow-up will need to be extended, the DMC and TSC recommended recruitment continue beyond the sample size of 2270 patients. Recruitment of up to an additional 900 participants (total 3170 participants) was completed in May 2023. This should ensure 97 primary outcome events are accrued in the standard care arm by August 2024.

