## Trial status

Recruitment began in September 2019 and has been completed on 11 May 2023. The trial opened using protocol v2.0, and the current protocol in use is v5.0.

Key amendments for the TARGET CTCA trial include:Amendment (September 7, 2020): Addition of new sites.Protocol Amendment v3.0 (March 25, 2021): Changes to data collection methods at sites, clarifications to Sect. 5.1 (identifying participants), Sect. 5.4 (withdrawals), Sect. 6.1.2 (scanning visit), Sect. 6.1.3 (management recommendations), Sect. 7 (assessments), and Sect. 8.2 (proposed analyses, introduction of COVID-19 test data).Amendment (August 4, 2021): Recruitment extension from September 1, 2021, to August 31, 2022, due to impact of COVID-19.Protocol Amendment v4.0 (July 7, 2022): Recruitment extension for 8 months until April 2023 and an increase in the recruitment target from 2270 to 3170.Protocol Amendment v5.0 (September 26, 2022): Introduction of a new lifestyle questionnaire at 24 months.

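### The stated minimum follow-up of 24 months does not fit a recruitment end of 11 May 2023 and an event target projected for August 2024

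*Protocol article*

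**What the plan says.** - **Follow-up length.** Long term follow-up assessments has all patients followed at least until the required number of events. It then states: "This is expected to be a minimum of 24 months for each participant and a median of 36 months". The abstract repeats the 36-month median, next to a sample size of 2270.
- **Recruitment.** Trial status: "Recruitment began in September 2019 and has been completed on 11 May 2023". Sample size calculation puts the extended total at 3170, up to 900 more than the 2270 planned.
- **Event target.** Sample size calculation, after describing the extension: "This should ensure 97 primary outcome events are accrued in the standard care arm by August 2024". The same paragraph gives an earlier planned follow-up date of September 2024 and says recruitment was extended so that follow-up would be less likely to need extending.
- **Closure.** Statistical analysis continues follow-up until 97 standard-care events and counts outcomes up to a common study end date, for which no date is given.
- **24-month endpoints.** SAQ-7 and EQ-5D-5L are sent at 3, 12 and 24 months after randomisation, with a lifestyle questionnaire at 24 months. Table 1 lists, for example, "Quality of life as assessed by the EQ-5D-5L up to 24 months of randomisation". Within-trial QALYs use the EQ-5D-5L data.

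**The concern.** Adding patients while holding the event target fixed brings the target forward and shortens follow-up, above all for the last recruits. The 24-month minimum and 36-month median nevertheless stand in the current text beside the later recruitment end and the August 2024 projection.

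The minimum follow-up is a design property that readers rely on. It tells them that every participant can contribute a 24-month questionnaire, and over what period the primary hazard ratio is observed. If the trial closes at the event target, late recruits have no 24-month SAQ-7, EQ-5D-5L or lifestyle data for administrative reasons, and the QALY inputs thin out in the same way.

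**Working it through.** **1. The plan's own figures reproduce.** Inputs from Sample size calculation: 9% in standard care, 5.4% under a 40% relative reduction, two-sided 0.05, 90% power.

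n = [1.960·√(2·0.072·0.928) + 1.2816·√(0.09·0.91 + 0.054·0.946)]² / 0.036² = 1081.4 per arm (stated: 1081).

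2162 × 1.05 = 2270 (stated: 2270). 1081 × 0.09 = 97.3 events (stated: 97). The target is therefore the expected standard-care count for the original 1081 per arm.

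**2. Minimum follow-up at August 2024** (date arithmetic; month = 30.4375 days).
- 11 May 2023 to 1 August 2024: 448 days = 14.7 months.
- 11 May 2023 to 31 August 2024: 478 days = 15.7 months.
- 24 months after the last randomisation: 11 May 2025, which is 253 to 283 days (8.3 to 9.3 months) after August 2024.

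**3. Participants under 24 months at 31 August 2024**, that is, randomised after 31 August 2022. The 1925 participants assessed on 25 April 2022 are taken as all those randomised by then, which leaves 3170 − 1925 = 1245 over the next 381 days.
- From the counts alone: anywhere from almost none to 1245 (39%).
- Linear accrual (assumption): 1245 × 253/381 = 827, or 26%. A cut-off of 1 August gives 29%.
- Cross-check: if the original 2270 were all in by 31 August 2022, the extra 900 are 900/3170 = 28%.

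**4. Median follow-up at 31 August 2024**, set by the 1585th randomisation. Most of the 1925 had under 12 months on 25 April 2022, so at most 962 were randomised before 25 April 2021.
- Bounds: the 1585th falls between 25 April 2021 and 25 April 2022, which gives 40.2 to 28.2 months.
- Linear accrual with 962 in by April 2021: (1585 − 962)/(1925 − 962) = 0.647 of the year, about 17 December 2021, giving 32.5 months.
- With 600 in by then (an assumed lower value, not in the article): about 21 January 2022, giving 31.3 months.
- A 36-month median needs 1585 randomised by 31 August 2021. That is about 148 a month from late April 2021, then 44 a month to April 2022, against 99 a month afterwards.

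**5. Power at 97 standard-care events.** Total events D = 97 × (2 − RRR), HR = 1 − RRR, power = Φ(√D/2 · |ln HR| − 1.96).

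| RRR | D | Power | Stated |
|---|---|---|---|
| 40% | 155.2 | 88.9% | 90% |
| 35% | 160.1 | 77.8% | 81% |
| 30% | 164.9 | 62.9% | 67% |

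For comparison, if all 3170 less 5% reached the 9% rate (1585 × 0.95 × 0.09 = 135.5 standard-care events), the two-proportion power would be 96.9%, 91.0% and 79.6%.

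**6. Timing of the trigger.** With a piecewise-constant hazard through the plan's rates (7.2% at 24 months, 9% at 36) and the accrual above, about 125 to 136 standard-care events are expected by 31 August 2024, with and without 5% loss. At those rates the 97th event comes earlier and follow-up is shorter still. The August 2024 projection therefore implies a lower rate than the design assumed.

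**The case against.** The case on the other side is that August 2024 is a projection and not a closing date. The follow-up section says at least until the target, the common end date is undated, and 24 and 36 months are worded as expectations. Keeping 97 events with more patients was a deliberate decision of the oversight committees. All of this is fair, and it rules out several stronger readings:

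- **That a 36-month median is impossible.** The documented counts allow 28 to 40 months. The accrual pattern it would need is odd but not excluded.
- **That a quarter of participants will miss the 24-month endpoints.** The 26% rests on assumed accrual. The questionnaires are timed from randomisation, and nothing says they stop at the event target. The article's text on withdrawal treats questionnaires and remote follow-up as separate. Table 1 also counts SAQ-7 and EQ-5D-5L up to 24 months, so earlier time points contribute.
- **That power is lost.** Power follows events, and the target keeps roughly what was planned. Longer follow-up would add power that the plan never promised.
- **That the analysis must wait for 36 months.** The words "with the treatment effect of the intervention apparent at 36 months" describe an earlier trial in stable chest pain and set no requirement here.

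What the objection does not remove is the conflict of dates. Statistical analysis does say that follow-up continues until 97 events, and on that reading the stated minimum is wrong. If a later closure is intended, the article does not say so.

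**Conclusion.** The stated 24-month minimum is inconsistent with the article's own dates if follow-up closes at the event target. The shortfall for the last participant is 8 to 9 months (14.7 to 15.7 against 24), and this part needs no accrual assumption. The share under 24 months (about 26%) and the median (about 31 to 32.5 months) are estimates under linear accrual, with wide documented bounds of 0 to 39% and 28 to 40 months.

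The likely origin is visible in Trial status. Recruitment was once due to end on 31 August 2022, and 24 months later is about the September 2024 follow-up date quoted in Sample size calculation. Recruitment then moved on by eight months and the follow-up sentence did not. That is an inference. The inconsistency stands without it.

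The primary comparison keeps about 89% power at the design effect. What is at stake is the accuracy of the stated follow-up, and the completeness of the 24-month endpoints and QALY inputs if collection stops at the trigger.

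**What to change.** 1. Restate follow-up for 3170 participants at the projected cut-off: a minimum of about 15 months, and the expected median computed from the actual randomisation dates (about 31 to 32.5 months on the assumptions above). This changes wording only.
2. Settle the 24-month endpoints in one of two ways. Either state that SAQ-7, EQ-5D-5L and lifestyle collection continues to 24 months after the last randomisation (about May 2025), whenever the event target is met. Or restrict the 24-month endpoints to those randomised at least 24 months before closure. The first costs about 8 to 9 more months of questionnaires if the target falls in August 2024. The second costs about a quarter of the 24-month sample, on linear accrual.
3. Optionally, if the 24-month minimum is to be kept for all outcomes, define the common study end date as the later of the event target and 24 months after the last randomisation. The downside is about 8 to 9 more months of remote follow-up, and more if the target is met before August 2024, which the plan's own rates would suggest. No added visits or patients are needed.

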**Table 2 Tab2:**
[figure not shown]
Schedule of assessments

^1^Performed either in ED/AMU or by phone

^2^To be taken if participants are uncertain of their pregnancy status

^3^As part of routine index hospital attendance

^4^Can be measured from surplus serum if not measured as part of routine hospital attendance

Data collection for outcomes will be performed by the research team at each site. All members of the research team involved in data collection will be appropriately trained and signed off by the site principal investigator on the delegation log as per Good Clinical Practice. All study data will be recorded on an electronic case report form held on a secure server. Data quality for all study outcomes will be monitored by the Edinburgh Clinical Trials Unit (ECTU) study database and data management team. Questionnaire completion will be encouraged with phone calls, letters or emails depending on the participants’ preference. Patients who subsequently decide to revoke their consent will be given the option to discontinue questionnaires or remote follow-up. This will be recorded as a change of status in the study database.

### Sample size calculation

Based on the event rate in the High-Sensitivity Troponin in the Evaluation of patients with suspected Acute Coronary Syndrome (High-STEACS) trial [19], myocardial infarction or cardiac death will occur in 7.2% of the study population at 24 months. The Scottish COmputed Tomography of the HEART (SCOT-HEART) trial [25] reported a 41% reduction in fatal and non-fatal myocardial infarction in those randomised to CTCA (hazard ratio 0.59 [95% CI: 0.41 to 0.81]), with the treatment effect of the intervention apparent at 36 months. It is anticipated that at a median follow-up of 36 months the event rate in the standard of care arm will be 9%. In the proposed study, for 90% power at an alpha of 0.05, 1081 participants will be required in each arm to detect a 40% relative risk reduction in the primary composite endpoint. To account for drop out of 5%, the aim is to recruit at least 2270 patients to the study. With this sample size, there will be 81% and 67% power to detect a 35% and 30% relative risk reduction if the intervention is less effective. Likewise, the sample size would have 99% power to detect a 50% relative risk reduction if CTCA is as effective in the study population as in those with stable chest pain [26]. With this sample size, it is estimated that 97 primary outcome events will be accrued in the standard care arm of the trial at a median follow-up of 36 months. The data monitoring committee (DMC) will review all primary outcome events intermittently and will inform the trial steering committee (TSC) when this target has been met.

On April 25, 2022, a blinded assessment of the number of events accrued in the first 1925 participants was undertaken and the DMC concluded the trial would not reach the number of primary outcome events required by the planned follow-up date of September 2024. This was a consequence of interruptions to recruitment due to COVID-19 with most participants having less than 12 months follow-up at this point. To minimise the likelihood that follow-up will need to be extended, the DMC and TSC recommended recruitment continue beyond the sample size of 2270 patients. Recruitment of up to an additional 900 participants (total 3170 participants) was completed in May 2023. This should ensure 97 primary outcome events are accrued in the standard care arm by August 2024.

